### Who will take informed consent? {26a}

Potential participants are invited via letters, phone calls, and/or personal communication at each site. Invitation letters include contact information for the study coordinator, who sends a link to the electronic consent form to families who contact him. Participants receive written information about the trial via this link and consent by signing the consent form electronically, using their personal identifying number and electronic ID (e.g., bank cards). Informed consent from one parent is required for children 8–16 years. Children above 16 years provide separate consent.

### Additional consent provisions for collection and use of participant data and biological specimens {26b}

No biological data are collected. For participants with a sibling with ND who is aged 16 and above, the sibling with ND has to consent for use of information about him/her (but not to family members joining the trial).

### Interventions

#### Explanation for the choice of comparators {6b}

Upon careful consideration of various potential comparator arms—a thorny issue in RCT research—we decided on a waitlist control design for three main reasons. First, waitlist represents a “treatment as usual” control comparator and provides an opportunity to demonstrate what the SIBS intervention adds to usual care. Second, empirical data that show how siblings’ well-being develops over time without intervention are lacking. Given that no care is the common scenario, a waitlist comparator is particularly reasonable at this stage of knowledge development. Third, it would be unethical to offer a comparator control intervention without robust preliminary outcomes, such as the SIBS intervention.

#### Intervention description {11a}

The intervention comprises 5 sessions delivered over 2 days, 1 week apart. Day 1 comprises sessions 1–3 (3.0 h including breaks). Day 2 comprises sessions 4–5 (2.5 h including breaks). Sessions 1, 2, and 4 are parallel (separate) group sessions for siblings and parents. Sessions 3 and 5 are integrated sibling-parent dialogs in which each sibling and parent talk together, separate from other participants. Two main themes, both empirically derived sibling challenges, provide the basic components of the intervention: disorder knowledge and emotional experiences. These themes are discussed in relation to the overarching component, family communication. Session 1 is the introduction. Sessions 2–3 focus on siblings’ ND knowledge. Sessions 4–5 focus on siblings’ emotional experiences based on cognitive-behavioral principles about how thoughts and behaviors influence emotions. In sessions 2 and 4, siblings generate lists of ND questions and challenges, respectively, which a group leader then brings to the parent group for discussion. In sessions 3 and 5, each sibling discusses their questions and challenges with their parent. The parent sessions focus on communication training focused on ND knowledge and siblings’ emotional challenges, introducing the SIBS motto “listen, explore, validate,” using standardized video examples of real sibling-parent dialogs with various degrees of open-exploratory communication as a basis for discussion. Parent sessions also comprise psychoeducation about sibling challenges and introduction to cognitive-behavioral principles about emotional coping. The SIBS intervention is outlined in a step-by-step manual for group leaders (see Fig. 1).

**Fig. 1 Fig1:**
[figure not shown]
Overview of the SIBS intervention

Each group is conducted by two group leaders. Thus, running the intervention requires four group leaders. In sessions 3 and 5, one group leader provides feedback to each of the sibling-parent dialogs, reinforcing open-exploratory communication. All sessions are videotaped. We measure group leader adherence with the Competence and Adherence Scale for Cognitive Behavioral Therapy (CAS-CBT) [13].

#### Criteria for discontinuing or modifying allocated interventions {11b}

Because the intervention is conducted over two half days, there are no explicit criteria for discontinuing or modifying the intervention. If a family does not show up on the second course day, or do not submit questionnaires, we attempt to continue to collect data from these participants to examine trajectories of change based on partial data.

#### Strategies to improve adherence to interventions {11c}

We measure group leaders’ adherence to the manual with an adapted version of CAS-CBT. We take the following measures to enhance group leader adherence: quality training of group leaders. The training of group leaders comprises a 1h e-learning program, which the group leaders can access from anywhere online. The e-learning program was developed in close collaboration with users, i.e., parents of children with disorders and health care providers. After completion of the e-learning program, potential group leaders submit a reflection note about the SIBS manual content. When the e-learning course is approved, group leaders are invited to a 2-day practical workshop. So far, we have been able to provide this training free-of-charge for participants. The 2-day training course comprises practical run through of all the group sessions, with practical role plays after watching example videos from the manual developers. Throughout the study period, we conduct 2–3 webinars per year, which all group leaders are invited to. The purpose of the webinars is to present and discuss potential challenging issues in group delivery.

In terms of participant adherence, the SIBS manual includes a task in which parents and siblings sign a contract specifying a date and time for when they will continue the dialog started during the intervention. At the 12-month follow-up, we ask participants to self-report whether this happened or not. We use this measure as a proxy for participant adherence in our analyses of long-term outcomes. We also ask participants to complete a “quiz” about the main components of the SIBS manual.

#### Relevant concomitant care permitted or prohibited during the trial {11d}

Given the inclusion key is being siblings/parents of children with ND who receive specialist or municipal health services, concomitant care is unavoidable and disallowing it would be unethical. We register concomitant care for siblings at all measurement points. The intent-to-treat sample will be compared with the per-protocol analyses excluding participants who have received concomitant care.

#### Provisions for post-trial care {30}

If clinical needs beyond the SIBS intervention are identified among participants (e.g., suicidality), site coordinators will assist families with adequate referrals. Patient rights according to specialist and municipal health legislation applies in terms of participant risks.

### Outcomes {12}

The primary outcome is sibling mental health, measured with the Strengths and Difficulties Questionnaire (SDQ) [14]. The 25-item SDQ is rated by siblings (self-report), as well as the participating sibling’s parents and main teacher, as proxy reports on sibling well-being. The SDQ covers five domains (emotional, conduct, inattention, peer problems, and prosocial behavior). We chose the SDQ as the primary outcome for the three main reasons. First, the SDQ has well-documented psychometric properties with this age group and substantial overlap with lengthier mental health measures (e.g., [15]). In our open trial, the SDQ showed good inter-item reliabilities (*α* = .77 to .82) and significant reduction from pre-intervention to 6-month follow-up, demonstrating good responsiveness to change. Second, the SDQ provides a continuous score and a clinical cutoff score. This enables us to report both mean change scores from pre-intervention to post-intervention, 3-, 6-, and 12-month follow-up, and the number of participants in the clinical, borderline, and normal range at each measurement point. Third, the SDQ includes strengths, an essential component for measuring well-being. Outcomes will be reported for sibling, parent, and teacher ratings.

Secondary outcomes cover additional risk factors for siblings linked to the World Health Organization’s well-being definition [16]: (1) family communication, because poor family communication is a documented risk factor in families of children with chronic illness [2]. It is measured with the Parent-Child Communication Scale (PCCS) [17], rated by siblings about parents and parents about siblings; (2) quality of life, because it represents a function-based indicator of well-being beyond mental health symptoms. It is measured with the KINDL Fragebogen [18] rated by siblings and parents (about siblings); (3) sibling adaptation, because it is a well-being variable tailored for siblings of children with chronic illness. It is measured with the Negative Adjustment Scale (NAS) [19], rated by siblings; and (4) sibling ND knowledge, because it is associated with sibling well-being [4]. It is measured with the Sibling Knowledge Interview (SKI) [6], conducted with siblings over the phone by trained clinicians. All secondary outcomes have demonstrated internal consistency (*α* = .90 for KINDL [18]; *α* = .75 to .82 for PCCS [11, 17]; *α* = .79 for NAS [6]; *α* = .78 for SKI [11]).

Predictor variables are as follows: (1) ND characteristics, because ND impairment is a consistent predictor of sibling well-being [1]. Parents report about the child with ND with the well-validated Developmental Behaviour Checklist [20]. We have ethical approval to collect patient record information for the child with ND, from which we obtain a ND impairment score (i.e., diagnosis, clinician’s severity ratings, and number of clinic appointments); (2) parent mental health, because it is a documented predictor of sibling well-being [3]. It is measured with the well-documented Symptom Checklist-90 [21] and with the Beck Depression Inventory, for a more specific depression measure [22]; (3) family stress, due to the documented strain for families of children with ND. It is measured with the Family Support Scale [23]; and (4) group leader manual adherence, because a limitation of previous sibling intervention studies is the lack of adherence data, and to identify manual components that may need to be added/enhanced after the project period. We measure it using an adapted version of the CAS-CBT [13] (see Table 2).

**Table 2 Tab2:**
[figure not shown]
Schedule of enrollment, interventions, and assessments

*S* siblings, *P* parents, *T* teacher, *O* observer, *C* clinician, *T*^*pre*^ pre-intervention, *T*^*post*^ after intervention/waitlist, *T*^*3m*^ 3 months after intervention, *T*^*6m*^ 6 months after intervention, *T*^*12m*^ 12 months after intervention

### Participant timeline {13}

Siblings and parents of children diagnosed with ND who receive municipal or specialist health services are invited. The intervention is delivered at municipal and specialist health service sites. The intervention is the only activity requiring site attendance (two visits). All sibling- and parent-rated measures are completed online (see Fig. 2 for participant timeline; see Table 2 for the overview of the measures, measurement points, and alignment with study objectives).

**Fig. 2 Fig2:**

Participant flow chart. T^pre^, pre-intervention; T^post^, immediate post-intervention. T^pw^, post-waitlist; T^3m^, 3 months post; T^6m^, 6 monhts post; T^12m^, 12 month post. *The main group difference to be examined here

### Sample size {14}

The planned sample is 288 siblings, 288 mothers, and 288 fathers. Based on a power analysis of change in the main outcome variable (SDQ) from our open trial, with a minimal relevant standardized effect size of 0.4, a statistical power of .8, and a significance level of .05 [24], we need a sample of 136 families. The intra-cluster correlation coefficient (ICC) in our open trial was 0.11. We have taken this lack of independence between observations into account in sample size estimates. The planned group size is 6, which results in an inflation factor (IF) of 1.55 (IF = 1 + (*m* − 1) × ICC) [25]. Adjusting with this IF resulted in a sample size of 211 (IF × 136). We further increased the sample to 288 to compensate for dropouts and concomitant care (estimated to 27% based on our open trial). An estimated 5000 children with ND aged 0–18 years receive health services in the catchment area, of whom an estimated 1000 (20%) have at least one sibling aged 8–16 years. Thus, a 29% response rate is required to reach our sample size. We believe this is a realistic goal given the response rate in our open trial was 58%, and whereas one site recruited 107 participants in our open trial, we now have eight sites.

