## Introduction

### Background and rationale {6a}

Sibling relationships, our longest lasting bonds, represent a unique source of learning, support, and rivalry. Chronic illness in children involves risk for reduced well-being among siblings [1]. The mechanisms behind this risk are associated with (1) the chronic illness itself (e.g., behavior problems), (2) siblings’ lack of illness knowledge (e.g., misunderstandings), (3) poor parental mental health due to extra care responsibilities, and (4) poor family communication (e.g., less open and warm communication [2–4]).

Previous sibling interventions have shown positive outcomes for siblings’ well-being (e.g., [5, 6]). However, systematic reviews have demonstrated that no intervention has an established evidence-base [7, 8]. Therefore, we plan to examine a group intervention for siblings and parents of children with chronic illness in a randomized controlled trial (SIBS-RCT). SIBS-RCT is based on preliminary studies conducted by our consortium. First, we conducted a qualitative study of group sessions for 58 siblings of children with rare disorders. We found that siblings have limited disorder knowledge [4], conflictual emotions and passive coping strategies [9], and unique perspectives on their brothers and sisters with disorders [10]. Based on user feedback and these preliminary findings, we developed the SIBS intervention, a 5-session manual-based program with parallel sibling and parent groups. A unique feature of the SIBS intervention is integrated sibling-parent dialogs, which we added due to evidence of poor family communication in families of children with chronic illness [2].

We examined the SIBS intervention in an open trial with 107 families of children with rare disorders, autism, congenital heart disease, cerebral palsy, or Down syndrome. We found significantly improved sibling mental health and family communication from pre-intervention to 6-month follow-up (mean effect size *d* = 0.43) [11]. Acceptability and feasibility were promising, with a 54% response rate, 86% group leader manual fidelity, and mean sibling and parent satisfaction scores of 3.6 on a 1–4 rating scale.

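### The stated inputs (effect 0.4 on change in SDQ, power .8, alpha .05) do not give 136 families for the planned two-arm comparison, and the shortfall carries through to 288

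*Protocol article*

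**What the plan says.** Sample size {14} of the protocol article bases its calculation on how the SDQ changed in the earlier open trial, and takes 0.4 as the smallest standardized effect worth detecting. It gives the other inputs and the result together: "a statistical power of .8, and a significance level of .05 [24], we need a sample of 136 families". The section gives no sidedness, standard deviation or pre-post correlation.

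It then allows for clustering, with an ICC of 0.11 and groups of 6: "Adjusting with this IF resulted in a sample size of 211". Finally it raises 211 to 288 for dropout and concomitant care, put at 27%.

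Two other sections fix what is being powered. Sequence generation {16a} sets 1:1 allocation in clusters of 6. Statistical methods {20a} makes the main effect the intervention–waitlist difference in SDQ from pre-intervention to 3 months, tested by mixed ANOVA.

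**The concern.** With two arms and two time points, the interaction in a mixed ANOVA is a two-sample test of change scores. An effect standardized on change enters that test directly, and effect, power and alpha then determine the sample size. The total that they determine is well above 136.

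The protocol relies on this calculation. Table 1 presents 288 siblings, based on a power analysis, as an advance over underpowered trials. Objectives {7} plans what to do if the arms do not differ: look for responding subgroups, rework the manual and avoid promoting a less-than-optimal intervention. If the chance of missing the minimal relevant effect is larger than the stated 20%, a null result says less against an effect of 0.4 than readers will assume.

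**Working it through.** **Inputs.** Effect d = 0.4, power 0.80, alpha 0.05, ICC 0.11, group size 6 and loss 27%, all from Sample size {14}; 1:1 allocation from {16a}; contrast and model from {20a}. Sidedness is not stated, so both are shown.

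**Step 1: the later steps reproduce.**
- Inflation factor: 1 + (6 − 1) × 0.11 = 1.55.
- 136 × 1.55 = 210.8, so 211.
- 211 / (1 − 0.27) = 289, against 288 (48 groups of 6).

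The discrepancy is therefore confined to 136, which these steps treat as a total over both arms.

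**Step 2: the first step does not.** The normal approximation per arm is n = 2(z_alpha + z_power)² / d².
- Two-sided: 2(1.960 + 0.842)² / 0.16 = 98.1. The t-test gives 99.08, so 100 per arm and **200 in total**.
- One-sided: 2(1.645 + 0.842)² / 0.16 = 77.3. The t-test gives 77.97, so 78 per arm and **156 in total**.
- Paired pre-post test: 52 two-sided, 41 one-sided.
- Reading 136 as a per-arm figure gives 91% power, and would not fit the later steps.

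**Step 3: power that 288 gives on the stated inputs.** Power is approximately Φ(0.4 × √(N/4) − 1.960), where N is the effective total. The t-test values are:

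| Scenario | Effective total | Two-sided power at 0.4 |
|---|---|---|
| 27% loss, factor 1.55 | 288 × 0.73 / 1.55 = 135.6 | 64% |
| 27% loss, groups shrunk to 6 × 0.73 = 4.38, factor 1 + 3.38 × 0.11 = 1.37 | 210.2 / 1.37 = 153 | 69% |
| No loss, factor 1.55 | 288 / 1.55 = 186 | 77% |

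For the first row the normal approximation is 0.4 × √33.9 − 1.960 = 0.369, and Φ(0.369) = 0.644. The effect detectable there with 80% power is about 0.48. One-sided power in that row is 75%.

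**Step 4: enrolment that the stated inputs imply.** By the protocol's own steps, 200 × 1.55 = 310 analysed and 310 / 0.73 = 425 enrolled. With the smaller factor, 200 × 1.372 = 274 analysed and 274.4 / 0.73 = 376 enrolled.

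**Step 5: what would make 136 right.** An added pre-post correlation r would do it.
- Baseline-adjusted analysis multiplies the total by (1 − r²). At r = 0.56, 200 × 0.686 = 137, and power at 68 per arm is 79.8%.
- Change scores with 0.4 in raw-SD units multiply it by 2(1 − r). At r = 0.66, 200 × 0.68 = 136, and power is 80.2%.

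No r is given. Over an assumed range of 0.3 to 0.7 (normal approximation), the required total falls from 180 to 102 with baseline adjustment, and from 276 to 118 for change scores in raw-SD units.

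**The case against.** The strongest reply is that a figure that cannot be reproduced need not be wrong. The section refers to change in the open trial and cites a method source. A calculation using open-trial data could include a pre-post correlation that a condensed article does not print, and either correlation in step 5 would give 136. This stands in part: the documents do not rule such a correlation out. It does not rescue the sentence as written. The effect is described on change, so no correlation is needed, and {20a} plans a mixed ANOVA, not a baseline-adjusted model. On the raw-SD reading an unstated correlation could also hurt: at r = 0.3, power at 68 per arm is about 50%.

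A second reply is that 64% is the low end. This stands. The 27% includes concomitant care, but {11d} and {20a} exclude those families only from the per-protocol analyses, so they remain in the intent-to-treat sample. A factor of 1.55 is also too large once loss has shrunk the groups. All three two-sided values are nevertheless below 80%. One-sided, the no-loss case would reach 86% and the shrunken-group case 79%, but no one-sided test is stated.

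A reader might also infer where 136 came from: a one-sided test at d = 0.43, the open-trial value in Background and rationale {6a}, gives exactly 68 per arm. The documents do not support this. That value is a mean effect size given with the finding "We found significantly improved sibling mental health and family communication from pre-intervention to 6-month follow-up", and is not identified as the SDQ effect. One-sided testing is mentioned nowhere. A match found after trying several combinations is not evidence of origin.

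**Conclusion.** Wrong as written. The stated inputs require about 200 families in total two-sided, or 156 one-sided, before clustering and loss, and the article states 136. The deficit passes unchanged into 211 and 288. On those inputs, two-sided power at 0.4 with 288 enrolled is about 64% to 77% depending on loss.

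This assumes a two-sided test, 0.4 standardized on change as the section says, ICC 0.11 and groups of 6. A reader might conclude flatly that the trial has 64% power and not 80%. That goes too far: 64% holds only with the full 27% loss and the unreduced factor, and an unstated correlation of about 0.56 or 0.66, used in the matching analysis, would restore 80%.

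**What to change.** Keep 288 and do one of two things in Sample size {14}.

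1. Restate the power: two-sided 5%, 288 enrolled, about 64–77% at d = 0.4 depending on loss, with 80% at about d = 0.48 under the planned 27% loss.
2. If the open-trial pre-post SDQ correlation supports 136, state that correlation and the sidedness, and make the primary model in Statistical methods {20a} the matching one: baseline-adjusted and allowing for clustering.

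The first costs a less favourable stated power. The second costs a change to the primary model as worded. Neither needs extra families.

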### Recruitment {15}

Participants are recruited from municipal and specialist health services from August 2019 to December 2022. At each site, a coordinator will send invitations to all families of patients with ND aged 0–18 years registered in the patient database. During the study period, families of all referred patients who meet the inclusion criteria will be invited. Posters/leaflets with study information will be displayed at site waiting rooms. Recruitment will be monitored through continuous registration in a database and monthly meetings between the PI and site coordinators. The main feasibility challenge to SIBS-RCT is recruitment delay, which we will endeavor to allay by advertising broadly and involving multiple sites. Families with ND experience considerable strain and may struggle to attend interventions. We add the following features to enhance attendance: (a) only one parent required, (b) group session times advertised early (all sites have set intervention dates throughout the study period), and (c) attendance certificates to document siblings’ school absence. Group leaders are also under strain due to service requirements. We add the following features to enhance group leader recruitment/retention: (a) free-of-charge training and supervision, including online support; (b) formal contracts with sites; (c) regular site visits; (d) collaboration across sites; and (e) a trained team of advanced psychology students who can step in at sites free-of-charge. If delays are severe, we may add sites and advertise via newspapers (already ethically approved).

### Assignment of interventions: allocation

#### Sequence generation {16a}

Participants are randomly assigned to either intervention or 12-week waitlist (1:1), in clusters of 6, stratified by participant age to avoid > 4-year age gaps between participants in the intervention groups. Each site requests a randomization number when the site has ~ 6 consenting participants within each age range. A pre-generated randomization indicates whether the cluster will be either intervention or waitlist. The allocation sequence was computer-generated by a research coordinator who is independent of the PI. The sites and participants are advised of their allocation approximately 2 weeks prior to group dates, to respect their time management needs (e.g., planning time off school and work for participants; allowing time for other clients for group leaders). Participants allocated to waitlist receive the intervention after 12 weeks. The dates for the potential waitlist groups are included in the original invitation letter to ease families’ planning.

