**Methods:**

We are conducting a randomized controlled trial comparing a five-session manual-based group intervention for siblings (aged 8 to 16 years) and parents of children with neurodevelopmental disorders to a 12-week waitlist, called SIBS-RCT. The intervention comprises three separate sibling and parent group sessions and two joint sessions in which each sibling talks to their parent alone. The intervention aims at improving parent-child communication and covers themes such as siblings’ understanding of the neurodevelopmental disorder, siblings’ emotions, and perceived family challenges. Participants are recruited through municipal and specialist health centers across Norway. The primary outcome is sibling mental health. Quality of life and family communication are secondary outcomes. Participants are block-randomized to the intervention or 12-week waitlist in groups of six. Measures are collected electronically at pre- and post-intervention/waitlist, as well as 3, 6, and 12 months post-intervention. The main effect to be examined is the difference between the intervention and waitlist at 12 weeks post. All outcomes will also be examined using growth curve analyses. We plan to include 288 siblings and their parents by the end of 2022.

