### Eligibility criteria {10}

The inclusion criteria are as follows: (1) being the sibling of a child diagnosed with ND who is aged 0 to 18 years and who receives specialist and/or municipal health services. The service-recipient criterion has been set to ensure ND impairment is in the clinical range, as ND impairment is a consistent predictor of sibling well-being [1]; (2) sibling age 8–16 years, to ensure generalizability across age spans. This age range was used in our open trial [11]. Sibling groups will be age-clustered to ensure a maximum 4-year age span from the youngest to the oldest participant; and (3) one parent able to attend the intervention. Families choose which parent. We applied this in our open trial due to the care needs of the child with disorder, with two thirds of participating parents being the mother (34% fathers). We collect data from both parents regardless of participation and encourage the participating parent to discuss the intervention with the non-participating parent. The follow-up questionnaire addresses the involvement of the non-participating parent, and we control for participating parent in all analyses of outcomes. If more than one sibling from the same family attends, both parents can participate.

The exclusion criteria for siblings are as follows: (1) being enrolled as primary patients in specialist health services and (2) ND diagnosis. Eligibility criteria for group leaders are as follows (1) employment in municipal or specialist health services, (2) trained as a health professional (e.g., nurse, social worker, special educator, psychologist); and (3) completion of a training package comprising a 5-session e-learning course (which takes about 1 h to complete) and a 2-day practical workshop. Throughout the data collection period, we invite all group leaders to supervision webinars 2–3 times per year. We also arrange regular site visits where practical matters and questions about the intervention are discussed.

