Across sites, the general procedure principle is that each site coordinator contacts the central project coordinator when they have at least 5 consenting participants. For each intervention group, 3–8 consenting families are required to allocate a randomization number. Participants receive all pre-intervention questionnaires approximately 1 month before the set group date, with regular reminders if not completed. Approximately 2 weeks before the set group date, families and group leaders are informed by the central research coordinator about whether the group was allocated to intervention or waitlist. If assigned to waitlist, participants receive the baseline questionnaires again 2 weeks before the intervention date (approximately 12 weeks after the initial group date). The aim is to conduct 48 groups over the project period. We have pre-generated a randomization list with 100 numbers, ensuring that there will never be more than 3 allocations to the same arm in a row (i.e., intervention or waitlist). This way, the number of participants in both arms will be somewhat balanced if we have to end the trial before reaching our aim of 48 groups, or if we need to increase the number of groups due to < 6 families per group (the aim is 288 families, i.e., 6 × 48).

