### Statistical methods

#### Statistical methods for primary and secondary outcomes {20a}

The main effect is measured as the difference between the intervention group and the waitlist group in SDQ scores from pre-intervention to 3 months, reported by siblings, parents, and teachers. This is investigated using mixed ANOVA, and effect sizes will be reported as Cohen’s *d*. To examine the effects beyond waitlist for the complete sample, we apply growth curve modeling, which enables us to investigate both mean changes at a group level over time and individual growth trajectories, with the inclusion of individuals with partial/missing data [26]. A series of linear mixed models are fitted. A model with only fixed and random intercepts serves as the null model, to which subsequent unconditional models of time will be compared. Finally, group membership and control variables are included in a set of conditional models, through which the longitudinal effect of the intervention is investigated. Growth curve models are fitted separately for the intent-to-treat sample and per-protocol, excluding participants with concomitant sibling care during follow-up. Multilevel analyses controlling for nesting (group and site level) are conducted with MPlus. Other analyses are conducted using updated versions of IBM SPSS and R.

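### The block-randomised and age-stratified labels do not match the allocation described, which does not secure balance by age, and the primary comparison names no age term

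*Protocol article*

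**What the plan says.** The abstract of the protocol article states: "Participants are block-randomized to the intervention or 12-week waitlist in groups of six". Sequence generation {16a} gives a 1:1 ratio in clusters of six and adds that allocation is "stratified by participant age to avoid > 4-year age gaps between participants in the intervention groups".

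The mechanics follow in three places:

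- Eligibility criteria {10}: "Sibling groups will be age-clustered to ensure a maximum 4-year age span from the youngest to the oldest participant".
- Sequence generation {16a}: "Each site requests a randomization number when the site has ~ 6 consenting participants within each age range", and then "A pre-generated randomization indicates whether the cluster will be either intervention or waitlist".
- Implementation {16c}: the team has "pre-generated a randomization list with 100 numbers, ensuring that there will never be more than 3 allocations to the same arm in a row". The reason given is to keep arm totals roughly even if the trial stops short of, or goes beyond, 48 groups. The same section allows three to eight families per group.

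On analysis, Statistical methods {20a} says of the main effect on the SDQ: "This is investigated using mixed ANOVA". It then introduces unnamed control variables for the conditional growth-curve models, and mentions multilevel analyses in MPlus that account for group and site nesting. Eligibility criteria {10} promises adjustment for the participating parent in every outcome analysis. Age is not named as a covariate anywhere.

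**The concern.** To a reader of trial reports, block randomisation means that arm totals are forced level at the end of each block. Stratification by age means that this is done separately within each age stratum. Those two terms are what readers and systematic reviewers will use to judge the randomisation. If the procedure delivers neither, the report will claim a protection against imbalance that the design does not give.

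It matters more here because the randomised unit is the group. There are 48 of them, and each is deliberately homogeneous in age, so one allocation moves about six children of similar age into the same arm. Adjustment for age in the primary comparison would make up for much of this, but the text names no such adjustment.

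**Working it through.** **1. The plan's own figure.** The inflation factor is 1 + (6 − 1) × 0.11 = 1.55, and 136 × 1.55 = 210.8, so 211. Allowing for 27% loss, 211 / (1 − 0.27) = 289.04, which is 290 for two equal arms against 288 stated. Finally 288 / 6 = 48 groups. The chain from 136 onwards reproduces within rounding, so 48 groups is the number to work with.

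**2. Labels against mechanics.**

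| Label | What the procedure text describes |
|---|---|
| Block-randomised in sixes (abstract) | Six is the cluster that receives a single allocation. No block size in the permuted-block sense is given. |
| Stratified by age ({16a}) | Age decides who is grouped together; the purpose stated in the same sentence is the age span inside a group. No list per age range is described. |
| Source of balance ({16c}) | One list of 100 entries with a maximum run of three, aimed at overall arm totals. |

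**3. Overall balance from a run-limited list.** The assumed algorithm is a fair draw at each entry with a forced switch after three equal entries. Exact recursion at 48 groups gives:

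- SD of the difference in groups between arms: 4.5 (simple randomisation: √48 = 6.9).
- Probability of exact balance: 18%.
- Difference of 4 or more groups: 50%. Difference of 8 or more: 11.5%.

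The rule therefore limits overall imbalance without producing block balance. The efficiency cost is small: a 20 v 28 split keeps 4 × 20 × 28 / 48² = 2240 / 2304 = 97% of the information.

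**4. Balance within age bands.** The article does not give the number of age ranges, so three equally common bands are assumed (48 / 3 = 16 groups each). A split of 2:1 or worse in 16 groups means 5 v 11 or more extreme, a difference of at least 6.

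- Exactly 16 groups per band, simulated: at least one band at 2:1 or worse in 40% of lists.
- Groups falling into bands at random, simulated: 44%.
- Hand check without the run rule: for one band, 2 × (1 + 16 + 120 + 560 + 1820 + 4368) / 65536 = 0.210; for at least one of three, 1 − (1 − 0.210)³ = 0.51. The run rule brings this down only to about 0.40.
- Two bands of 24: a difference of 6 or more groups in at least one band in 37% of lists.
- Separate blocks of four within each band: the within-band difference at 48 groups is 0.

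With band mid-ages of 9.5, 12 and 14.5 (assumed), the arms differ in mean age by more than one year in about 9 to 11% of lists.

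**5. What adjustment could gain.** In 1.55 = 6 × 0.11 + 0.89, the between-group part is 0.66. If age band explained none of it, nothing is gained. If it explained all of it, the variance of a group mean would fall by 0.66 / 1.55 = 43%. These are outer limits, and they assume that the 0.11 applies to change scores. The document gives no association between age and SDQ change, so the gain cannot be placed within them.

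**6. Form of the age term.** The primary effect is the arm-by-time contrast. An age main effect absorbs differences in SDQ level only; chance imbalance matters here through age-related differences in change, so the interaction of age with time is needed.

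**The case against.** The age sentence carries its own explanation: it says the purpose is to avoid wide age gaps within groups, and nowhere promises arms balanced on age. The abstract can likewise be read as using block to mean the group of six, and Implementation {16c} discloses the run-limited list and claims only rough balance. On that view this is loose terminology. That is a fair account of how the wording arose, but both words have settled technical meanings that the described procedure does not meet, and the abstract is read alone.

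Four stronger readings are tempting and are not supported:

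- *That no blocking or stratification took place.* The article gives one property of the list, not its generating algorithm, and a journal article condenses the full protocol. Undisclosed blocks or sub-lists cannot be ruled out.
- *That stratification by site is missing.* It was never claimed, so its absence contradicts nothing.
- *That site goes unadjusted, or that the primary comparison has no covariates.* Statistical methods {20a} mentions multilevel control for group and site, and Eligibility criteria {10} promises control for participating parent. What is unclear is whether the multilevel sentence reaches the mixed ANOVA.
- *That chance imbalance biases the result.* Under valid randomisation it does not, and ordinary inference allows for it. The primary measure is also change from baseline, which removes stable age differences in SDQ level. The loss is in precision and face credibility.

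Silence on an age covariate would alone be weak, since covariates are commonly left to the analysis plan. It counts here because groups are formed by age and the text calls age a stratification factor, which a primary model would normally reflect.

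**Conclusion.** The point holds as a mismatch between label and procedure, with a cheap improvement to the analysis attached. As described, the trial is a cluster randomisation of age-homogeneous groups from a single run-limited list. The terms used in the abstract and in Sequence generation {16a} imply balance, by age in particular, that this procedure does not secure. With three equal age bands, the chance of at least one band splitting 2:1 or worse over 48 groups is about 40 to 44%. That figure rests on the assumed number and frequency of bands and on the assumed list algorithm. Overall arm imbalance is a minor matter.

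The comparison remains valid. What is at stake is an accurate account of the randomisation, and precision that an age term could recover by an amount the document does not allow one to state.

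**What to change.** 1. In the abstract and Sequence generation {16a}, describe the allocation as cluster randomisation of groups formed within age ranges, drawn from a single list with at most three consecutive allocations to one arm. If permuted blocks or age-specific lists were in fact used, disclose them in Implementation {16c} instead.
2. In Statistical methods {20a}, include sibling age (or the group's age band) and its interaction with time in the primary comparison from baseline to 12 weeks.
3. In the same section, state that this comparison is covered by the multilevel model for group and site already mentioned.

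The cost is one or two extra parameters, no new data (age is known for every group when it is formed), and a slightly less favourable description of the randomisation.

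Two further steps are not needed. Fixed site effects would use 7 to 9 parameters (8 or 10 sites, less one) out of 48 clusters, and any site with all its groups in one arm would then add nothing to the contrast. Regenerating the list would alter allocation after inclusion began in September 2019.
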